The main aim of this study is therefore to determine the effects of a multifaceted approach on patient-centeredness, patients’ QoL and levels of distress by: investigating the *effectiveness* of a multifaceted approach for care improvement on patient-centeredness, patients’ QoL and levels of distress; identifying *determinants*, at both patient and clinic levels, of an increase in the level of patient-centeredness, an increase in patients’ QoL and a decrease in distress levels; and performing a *process evaluation* to study the feasibility of the multifaceted approach and gain insight into factors that affected the impact of the intervention.

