### Study population

The study will be performed in a representative Dutch infertile patient group, under treatment in one of 32 Dutch clinics. All couples that participate in this study underwent at least one cycle of medically assisted reproduction (for example, ovulation induction, intra-uterine insemination, IVF, and intra-cytoplasmic sperm injection). Both women and their partners will be invited to participate in this study individually. However, because it is still unknown whether women and partner experiences with patient-centered fertility care are associated, only the women’s data will be used to answer our main research questions. Partners’ data will be used to analyze whether gender is a determinant of patient-centered fertility care. Those couples who are pregnant while completing the questionnaire set will be excluded from all analyses, because most questions about patient-centeredness, patients’ QoL and levels of distress are confounded in this patient group
[18,27,28].

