### Determinants of change in patient-centeredness, patients’ QoL and distress levels

#### Patient characteristics

The following patient characteristics will be collected, based on general and fertility literature as possibly being associated with patient-centered care, QoL and/or levels of distress: gender, age, ethnicity, level of education, duration of relationship, economic status, duration and cause of infertility, fertility treatments so far received, consumption of professional emotional support during fertility treatment, medical history, and recently experienced lifetime events (for example, death of a relative, being fired from work)
[18,43-46].

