### Sample size calculation

To account for a representative number of patients per clinic (that is, 25 to 75 patients per clinic) at least 1,600 couples will be included. The sample size calculation, which was based on the results of the previous Patient-centredness Questionnaire validation study
[18], confirmed that this number of patients is sufficient for a proper analysis. To detect a mean difference score of 0.25 between usual care and the multifaceted approach on patient-centeredness (α = 0.05, two-sided testing, β = 0.8) at least 93 couples are required. Taking into account clustering of couples (30 couples/clinic) and a mean intracluster correlation coefficient of 0.13
[18], 1,023 couples have to be involved. With an expected response rate of 70%
[18], at least 1,462 couples have to be invited at both baseline and after measurement.

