#### Determinants of change in patient-centeredness, patients’ QoL and distress levels

First, all independent variables concerning baseline patient and clinic characteristics will be checked for colinearity. These variables include all patient and clinic background characteristics, as well as the four variables concerning hospital culture, and the team characteristics collected during EOV.

If a correlation coefficient >0.6 is found between two variables, preference will be given to the variable theoretically closest to actual outpatient performance. Subsequently, all independent variables will be tested in a univariate analysis with the dependent variables concerning the differences between patient-centeredness, patients’ QoL and levels of distress in baseline and after measurement. The variables tend to be associated and show enough interclinic variation will be included in three multilevel linear regression models to explain differences in an increase in patient-centeredness, an increase in patients’ QoL and a decrease in levels of distress, respectively. To assess which part of the variation can be explained by the determinants, the explained variance (*R*^2^) per model will be calculated. Significance for all analyses will be set at *P* <0.05.

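### The entry rule for the determinant models asks patient-level candidates to vary between clinics, which can keep associated patient-level determinants out of the adjusted models and the R²

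*Protocol article*

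**What the plan says.** The determinants part of the Data analysis section of the protocol article sets out a sequence. Candidates are first screened for collinearity. Their scope is wide: "These variables include all patient and clinic background characteristics, as well as the four variables concerning hospital culture", together with the team characteristics recorded at the outreach visits. Next, "all independent variables will be tested in a univariate analysis with the dependent variables", which are the differences between the baseline and after measurements. Finally, "The variables tend to be associated and show enough interclinic variation will be included in three multilevel linear regression models", one model each for patient-centeredness, quality of life and distress, and R² is calculated per model. The two entry conditions are joined by an and. No statistic or threshold is given for the second, and patient-level candidates are not exempted.

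The Background states the aim as determinants "at both patient and clinic levels, of an increase in the level of patient-centeredness", and likewise for quality of life and distress. The list under Patient characteristics begins "gender, age, ethnicity, level of education, duration of relationship, economic status". The Study population section reserves the main research questions for the women's data and adds, in a separate sentence, "Partners’ data will be used to analyze whether gender is a determinant of patient-centered fertility care".

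**The concern.** The second entry condition suits one kind of candidate and is applied to both. A clinic characteristic takes one value per clinic, so if clinics do not differ on it, nothing can be learned about it. A patient characteristic takes different values within a clinic, and a multilevel model uses those differences. Whether its average also differs between clinics has no bearing on whether its effect exists or can be estimated.

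At stake is the content of the three adjusted models. An associated patient characteristic that is spread evenly over clinics would be missing from them and from the R². Selection among patient characteristics would then depend partly on how uneven the case mix is, rather than on association with the outcome.

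**Working it through.** The plan gives no figure for this rule, so there is none to reproduce. The check is whether the condition is needed for estimation, and how the one candidate whose distribution is set by design would fare.

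**1. What the estimate needs.** For a covariate x in a model with clinic effects, the within-clinic estimate of its slope has variance

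Var(b) = σ²(within) / Σ(x − clinic mean of x)².

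The denominator involves only differences inside clinics.
- Clinic-level x: each x equals its clinic mean, so the sum is 0. All information must come from between clinics, and the condition is sensible.
- Patient-level x with the same distribution in every clinic: the sum is large although between-clinic variation is nil.

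**2. Gender as the worked example.** Inputs from the article: 32 clinics (Study design), 30 couples per clinic (Sample size calculation), both members of each couple invited (Study population). Partner response is not given, so it is assumed.
- Full partner response: 30 women and 30 partners per clinic. The within-clinic sum is 30 × 30 / 60 = 15 per clinic, and 32 × 15 = 480 in total.
- 70% partner response (assumed): 30 women and 21 partners. 30 × 21 / 51 = 12.35 per clinic, and 32 × 12.35 ≈ 395 in total.

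So there is ample within-clinic information in both cases.

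**3. Between-clinic variation of gender.** With full response every clinic is exactly half women, so the between-clinic mean square is 0. The ANOVA estimate of the intracluster correlation is then −1/(60 − 1) = −0.017, that is, nil. With incomplete response, simulation (2,000 runs, 30 women per clinic, binomial partner response, clinic-to-clinic spread on the logit scale; response and spread both assumed) gave these mean estimates:

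| Partner response | Logit SD between clinics | ICC of gender |
|---|---|---|
| 70% | 0 | −0.016 |
| 70% | 0.5 | −0.011 |
| 70% | 1.0 | 0.005 |
| 50% | 0.5 | −0.002 |
| 50% | 1.0 | 0.025 |

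**4. Reading the table.** If a 5% F test were taken as the threshold (an assumption), F ≈ (1 + (m − 1) × ICC) / (1 − ICC), with m the mean number of respondents per clinic and a critical value of about 1.46.
- 70%, SD 1.0: m = 51, F ≈ (1 + 50 × 0.005) / 0.995 = 1.26, below the threshold.
- 50%, SD 1.0: m = 45, F ≈ (1 + 44 × 0.025) / 0.975 = 2.15, above it.

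Gender would thus be expected to fail except where partner response is both low and very uneven. In that case it would pass because of response patterns, which say nothing about whether gender matters.

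**5. Passages side by side.** The aim covers the patient level. The candidate list contains patient characteristics. The entry rule makes no distinction between levels. Nothing in the article limits the rule to clinic-level candidates.

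**The case against.** The strongest objection is that change may exist only at clinic level. Study design has each clinic draw a new patient list for the after measurement, participation is anonymous, and no cohort of the same patients is described. If change is one value per clinic, a patient characteristic can explain it only through the clinic's mix, and a between-clinic condition is coherent. This does not rescue the rule. The article specifies multilevel regression for these models, which needs outcomes below clinic level, and the effectiveness section adjusts for patients clustered in clinics.

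The objection does remove some tempting figures. From "a mean intracluster correlation coefficient of 0.13" a reader might infer that 1 − 0.13 = 87% of the variance lies within clinics and that a patient-level effect would be detected with essentially 100% power. That coefficient belongs to the questionnaire score in the sample size calculation and is not shown to apply to change. A reader might also simulate a covariate independent of clinic, take a 5% test as the threshold, and find it dropped in 95% of runs. That only restates 1 − 0.05 and says nothing about the actual candidates.

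Three further points stand:
- Patient variables whose mix differs between clinics can pass. Treatments received are a plausible case, since Setting describes clinics that offer different treatments.
- All candidates are tested univariately before the rule applies, so a dropped variable has not gone untested, and nothing says it would be reported as irrelevant.
- A condensed article may leave the meaning of enough to the full plan. That excuses the missing threshold, but not a condition stated for patient-level candidates.

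**Conclusion.** The point holds in limited form. As written, the rule can keep associated patient-level determinants that are similarly distributed across clinics out of the three adjusted models and their R², against the aim of finding determinants at both levels. How many candidates would be affected cannot be stated, because the threshold is undefined and the article does not give their distribution by clinic.

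Two stronger readings are not supported. The rule does not remove patient-level determinants as a class. Nor is there an established contradiction over gender: the Study population section may intend a separate analysis on partners' data, and if the determinant models use women only, gender is constant and absent for that reason. What can be said is that gender, if run through these models, would be expected to fail the rule by design, subject to the assumed partner response above.

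The consequence is confined to the determinants aim. The randomised comparison does not use this entry rule.

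**What to change.** Change the entry sentence so that the between-clinic condition applies only to clinic-level candidates: clinic background characteristics, culture variables and outreach-visit team characteristics. Let patient-level candidates enter on association alone. Add a statement of the model and data set in which gender is tested.

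The cost is a revised sentence and a few more terms in the determinant models. Data collection and the effectiveness analysis stay as they are.

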#### Clinic characteristics

Potential determinants at the clinic level will be collected by a professionals’ questionnaire during patients’ baseline measurement and by separate data collection during the EOV. The questionnaire will be spread electronically among all healthcare professionals (for example, gynecologists, residents, nurses, laboratory employees, secretaries, and so forth) working at the fertility departments of the 32 participating hospitals. The questionnaire consists of two parts: 12 general questions about clinic characteristics (for example, number of fertility consultations per year, composition of the fertility team, mean age and sex ratio of the fertility team); and six questions from the Organizational Culture Assessment Instrument, a validated questionnaire to examine organizational culture based on the Competing Values Framework
[47-49]. The Competing Values Framework recognizes that no hospital exhibits only one culture, but that multiple cultures and values coexist simultaneously
[50] (that is, clan/family culture, adhocracy culture, market culture, and hierarchy culture). The four culture types relate to each other on a two-by-two matrix with two axes denoting both the flexibility and the orientation of the hospital to the outside world
[47-49,51-53]. In this study the validated Dutch version of the Organizational Culture Assessment Instrument will be used
[54].

Additional possible determinants at the clinic level of a change in patient-centeredness, patients’ QoL and distress levels will be collected during the EOV. According to the literature, these characteristics may influence successful implementation of the action plan – such as, for example, the level of preparation before and the enthusiasm and agreement of the professional team during the EOV
[55]. The researcher will record these team characteristics on a five-point Likert scale.

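### The determinants analysis tests 27-28 or more candidates on three outcomes at an unadjusted P<0.05 and reports R-squared from the same data, so chance determinants are likely and a clinic-level R-squared would be optimistic

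*Protocol article*

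**What the plan says.** The rule is in the protocol article under Data analysis, Determinants of change in patient-centeredness, patients' QoL and distress levels. It has four steps.

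1. Prune for collinearity: "If a correlation coefficient >0.6 is found between two variables", only one of the pair is kept.
2. Screen: "all independent variables will be tested in a univariate analysis with the dependent variables", which are the changes in the three outcomes.
3. Select and refit: "The variables tend to be associated and show enough interclinic variation will be included in three multilevel linear regression models". No numeric cut-off is given for either condition.
4. Report: "To assess which part of the variation can be explained by the determinants, the explained variance" is calculated for each model. The threshold is general: "Significance for all analyses will be set at" P<0.05.

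The candidates are described in two earlier sections. Patient characteristics opens with "The following patient characteristics will be collected, based on general and fertility literature as possibly being associated with patient-centered care" and lists 12 items. Clinic characteristics gives "12 general questions about clinic characteristics" and a culture instrument, which yields four scores. Team characteristics recorded at the educational outreach visit (EOV) are added to these. Identifying determinants is a declared aim in the Background.

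**The concern.** Selection, significance testing and explained variance all use the same patients and clinics. The rule makes no allowance for the number of candidates tested or for the model having been chosen by looking at the outcome. The final P-values and R-squared would then be read as if each model had been fixed in advance.

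The stake is the second aim. Readers will want to know which features of patients and clinics go with improvement, and how much they explain. If chance alone often produces a positive answer, some reported determinants may be noise, and the explained variance may look better than it would in new clinics. The Discussion expects the study's results to help improve care.

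**Working it through.** The article gives no candidate total, error rate or R-squared for this analysis, so there is no stated figure to reproduce first.

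**Inputs from the article**
- Patient candidates: 12 (Patient characteristics), or 11 without gender, because Study population answers the main questions with women's data only and studies gender with partners' data.
- Clinic candidates: 12 general questions and 4 culture scores (Clinic characteristics; Data analysis).
- Total: 12 + 12 + 4 = 28, or 11 + 12 + 4 = 27. At least three EOV items (preparation, enthusiasm, agreement) would make 31, but these exist only for clinics that had a visit.
- Clinics: 32 (Study design). Respondents required: 1,023. ICC: 0.13 for patient-centeredness (Sample size calculation).
- Outcomes: 3. Threshold: 0.05.

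**Assumptions**
- Each general clinic question is one variable.
- The ICC of 0.13 applies to all outcomes.
- The screening cut-off is 0.05, 0.10 or 0.20.
- Correlations are as shown in the table.

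**Step 1: univariate tests, independent candidates, no true determinant**
- One outcome: 1 − 0.95^28 = 76.2%. With 27 candidates: 1 − 0.95^27 = 75.0%.
- Three outcomes: 28 × 3 = 84 tests, and 1 − 0.95^84 = 98.7%.
- Expected false positives: 84 × 0.05 = 4.2.

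**Step 2: final models after screening, simulated with no true determinant**

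The table gives the chance of at least one P<0.05. Three values in a cell are for cut-offs 0.05 / 0.10 / 0.20.

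| Set-up, 32 clinics | One model | Three outcomes |
|---|---|---|
| Random intercept, 28 independent candidates, 18-52 respondents per clinic | 66 / 66 / 61% | 96 / 96 / 94% |
| Same, with a screen that ignores clustering | 51 / 59 / 59% | 88 / 93 / 93% |
| Random intercept, 27 independent candidates | 61-62% | about 94% |
| Same, candidates correlated 0.3 | 39-50% | 77-88% |
| Random intercept, candidates correlated 0.3 and outcomes 0.5 | 40-47% | 77-83% |
| Clinic as unit, 28 candidates correlated 0.2 and outcomes 0.5, pruned at r>0.6 | 54 / 46 / 49% | 89 / 82 / 84% |
| Random intercept, all 28 independent candidates, no screen | 67% | 96% |

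For independent outcomes the last column follows from the one before it: 1 − (1 − 0.66)^3 = 0.96, and 1 − (1 − 0.39)^3 = 0.77. Other runs with 28 independent candidates gave up to 68% per model and 97% across three outcomes.

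The last row isolates the cause. With every candidate fixed in advance and no screen, the rate is about the same, so the excess comes from the number of unadjusted tests.

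**Step 3: the between-clinic filter**

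The requirement for enough variation between clinics has no number, so it was not simulated. As a limiting case, suppose it removed all patient-level candidates and left 16. With the clinic as the unit, the rates are then 47-53% per model and 85-90% across three outcomes if independent. With correlations of 0.2 and 0.5 they are 36-44% and 70-80%.

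**Step 4: mean R-squared with no true determinant, cut-offs 0.05 / 0.10 / 0.20**
- Clinic level, random-intercept models: 0.10 / 0.17 / 0.26 in one set-up and 0.13 / 0.22 / 0.32 in another (true value 0).
- Clinic level, with a screen that ignores clustering: 0.32 / 0.36 / 0.39.
- Total, about 1,000 women: 0.02 / 0.03 / 0.05.

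**The case against.** A reader might infer that a false determinant is found more than 90% of the time, that outcome-based screening causes it, and that the explained variance will be sizeable. The article does not support any of these without qualification.

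- **Over 90%.** This is the joint figure for three outcomes, mostly with independent candidates. With modest correlation it falls to 77-89%, and the rate for a single model is much lower.
- **The screen as cause.** With no screen the rate is 67% per model, so multiplicity drives it.
- **Sizeable R-squared.** This holds only at clinic level. Total R-squared is 0.02-0.05, below the 0.086 found when all 28 candidates are fitted without a screen. The article specifies multilevel models and does not say which R-squared it means. The clinic-level reading is plausible, because patients are sampled anew after a year, so within-patient change is generally unavailable.

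Three further objections have weight. The patient candidates come from prior literature, so a complete absence of true determinants is an extreme scenario. The Discussion's remark about using the results covers the whole study and commits no clinic to act on a single determinant. Penalisation and validation are also details that a condensed article may leave to a fuller plan.

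The last objection does not remove the point. The article fixes the sequence of screening, refitting and reporting, together with one threshold for all analyses, for a declared aim that it does not label exploratory.

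**Conclusion.** The point holds in limited form. With 27-28 candidates and no true determinant, the written rule gives at least one significant determinant in roughly 40-66% of single models and in about 77-96% of trials across the three outcomes. Both are far above 5%, and the screen does not cure this. They remain far above 5% even in the limiting case of 16 candidates.

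If R-squared is reported at clinic level, its mean would be about 0.1-0.3 when the truth is 0. If total R-squared is meant, the inflation is small, about 0.02-0.05.

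The ranges rest on the assumed cut-off, correlations, common ICC and one variable per clinic question. The defect is confined to the determinants aim. The effectiveness comparison is a separate analysis and is not affected.

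**What to change.** In the determinants part of Data analysis:

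- Keep the candidate list, but repeat the whole prune, screen and fit procedure in a bootstrap that resamples clinics. Report optimism-corrected R-squared, giving clinic-level and total values separately, and how often each determinant is selected.
- Apply a multiplicity adjustment, such as Holm or false discovery rate, per outcome. Count all candidates tested, not only those that survive the screen. For scale, Bonferroni within one outcome uses 0.05/28 = 0.0018 and gives 1 − (1 − 0.0018)^28, about 4.9%, for independent univariate tests. Over three independent outcomes that leaves 1 − 0.951^3, about 14%, so the text should state that the adjustment is per outcome.
- Present the determinants as hypothesis-generating.

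A penalised multilevel model over the same candidates is an optional alternative to the screen. The cost is more analysis work, lower reported R-squared and fewer determinants claimed. No new data are needed.
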